### Analyses and reporting of results

#### General outline of analysis

The intention-To-Treat (ITT) population will consist of all eligible participants who gave consent and have been allocated to one of the two treatments, irrespective of treatment received. The per protocol population is defined as all participant who received the allocated treatment. The per protocol population includes those who initiated treatment for GDM as allocated following randomization and who completed the treatment until delivery, as well as those receiving normal antenatal care after having been allocated to the normal antenatal care group. If, in the course of normal antenatal care, a repeat OGTT was deemed necessary, and this repeat OGTT indicated a diagnosis according to both old and new GDM criteria, GDM treatment should be initiated as a part of normal antenatal care, and would not be a reason for a participant to be excluded from the per protocol analyses.

Participants who did not initiate GDM treatment when they had been allocated to GDM treatment, will be removed from the per-protocol population.

#### Planned analyses

Baseline characteristics will be presented as frequencies and percentages in each group, or as averages (mean or median) with standard deviations or interquartile ranges as appropriate. The primary outcome will be evaluated by estimating the relative risk between both treatment arms. Analyses will be conducted in both the intention-to-treat and per protocol population for the primary outcome.

Relative risks will be estimated for categorical outcomes, with 95% confidence intervals, and χ2 tests for significance. Fisher’s exact test will be used for sparse events where assumptions of the χ2 test are not met. Continuous data will be described as means with standard deviation if normally distributed, or medians with interquartile ranges when not normally distributed; tests for significance are t-tests or Mann-Whitney U tests, respectively. The Hodges-Lehman estimator will be used to calculate the confidence interval for the difference in medians.

Individuals who were randomized to normal obstetric care but for unknown reasons received treatment they will be excluded from the per protocol analysis. If the treatment followed an abnormal repeat OGTT they will remain in the per protocol analysis. Individuals who were randomized to GDM treatment but for unknown reasons never received treatment will be excluded from the per protocol analysis. If, per example, they did not receive treatment because of preterm birth they will remain in the per protocol analysis.

Subgroup analyses will be performed for BMI (under or above 30 kg/m2), early or late GDM (before or after 24 weeks) and according to the result of the OGTT (abnormal fasting result, abnormal postprandial result, or both).

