**Methods:**

The TANGO-DM trial is an open label, multicenter randomized controlled trial. Participants are pregnant with a gestational age between 16 + 0 and 32 + 0 weeks, who underwent a 1-step venous 2- or 3-point 75-gram oral OGTT, were eligible if they had glucose concentrations discordant between the old (1999) and the new (2013) criteria. After informed consent, women are randomized to either intensive GDM treatment, consisting of dietary advice and glucose monitoring and, if euglycemia is not reached, antihyperglycemic agents, or normal obstetric care without GDM treatment. The primary outcome is large-for-gestational-age infants (birth weight > 90th percentile). Secondary outcome measures include maternal complications, obstetric complications, neonatal complications, obstetric interventions, quality of life, and healthcare and societal costs. Outcomes will be analyzed according to the intention-to-treat principle. The study is powered to detect a reduction in LGA from 16% in the untreated to 10% in the treated group, which requires 1032 participants (516 per arm; alpha-error 5% for 80% power).

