#### Questionnaires

For all participants in the Tango-DM trial, questionnaires will be administered at 3 time points: study inclusion, around 36 weeks of pregnancy and 4–6 weeks postpartum.

Quality of life will be measured using the EuroQol (EQ-5D-5 L) at a gestational age of 36 weeks and 6 weeks post-partum. The EQ-5D-5 L assesses 5 domains (mobility, self-care, usual activities, pain/discomfort, anxiety/depression) with 5 possible answer levels ranging from “no problems” to “severe problems” [26].

Mood will be scored using the Edinburgh Postnatal Depression Scale (EPDS) at inclusion and post-partum. The EPDS has 7 questions regarding depression and anxiety [27].

The questionnaires will take approximately 10–30 min to complete.

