#### Randomization

Randomization to the intervention arm or comparator arm will be done on a 1:1 basis, using the online software tool Castor EDC (www.castoredc.com, Castor EDC, Ciwit B.V., the Netherlands and Castor Research Inc, USA). Castor EDC complies with all applicable laws and regulations. Block stratified randomization will be used, with stratification for center and alternating variable block lengths of 2 and 4 with a block size unknown to the site. The trial is not blinded: health care providers and participants will be aware of their OGTT results and their allocation group.

We will register age, parity, prepregnancy BMI, prior GDM and ethnicity for women not consenting to randomization in the TANGO-DM trial.

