### Sample size

In the planning phase of the study, we initially calculated a sample size of 2,520 participants (1,260 per group). This would generate sufficient power to detect a reduction of the primary outcome LGA from 14% in the group randomized to normal obstetric care to 9.8% in the group randomized to intensive GDM treatment among participants (alpha = 0.05, beta = 0.2). The assumed prevalence of LGA in the group randomized to normal obstetric care was based on the RESPECT study [36], in which a 5% prevalence of GDM was found in a cohort of patients from midwifery practices and secondary and tertiary hospitals in the Utrecht region of the Netherlands, according to the old (1999) criteria. The prevalence of LGA among women with GDM in the RESPECT cohort was 19%. Reasoning that the prevalence of LGA in women with a discordant OGTT results is likely to be lower than the mean for GDM patients, but higher than the general population (e.g. 10%) led us to an estimate of 14% in women without treatment. This estimate is confirmed by unpublished analyses within the RESPECT cohort, which found a 16% prevalence of LGA among discordant cases.

However, the subsequently published GEMS trial [13], which contained data on the LGA prevalence in discordant cases, triggered our power recalculation. The population in the sub-analyses of the GEMS trial with discordant test results was more similar to the population in the TANGO-DM than the previously used numbers of the RESPECT cohort. The prevalence of LGA in women with untreated mild hyperglycemia in the GEMS trial was 18.0% compared to 6.2% in the treated group. We therefore used a background incidence of 16% LGA (instead of the earlier 14%) in untreated women, to demonstrate or refute a reduction of LGA to 10% in participants who are treated and a 5% correction for women who are lost to follow up, we need 1032 participants (516 per group). The recalculation of the sample size was not informed by interim data of the TANGO-DM trial. The adjustment was approved by the Medical Research Ethics Committee of the Amsterdam UMC, and changed in the trial registration.

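### The primary LGA analysis uses neither the randomisation stratum (centre) nor the collected baseline variables: it is valid, but gives up a modest amount of precision

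*Protocol article*

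**What the plan says.** The Randomization section of the protocol article states: "Block stratified randomization will be used, with stratification for center". Allocation is 1:1, with blocks of 2 and 4.

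For the analysis, the Planned analyses section says "The primary outcome will be evaluated by estimating the relative risk between both treatment arms". For categorical outcomes in general it adds "Relative risks will be estimated for categorical outcomes, with 95% confidence intervals", tested by chi-square, or by Fisher's exact test where events are sparse. It names no centre term, stratified test or covariate for the primary outcome.

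The Baseline characteristics section lists, among others, prepregnancy BMI, parity, risk factors for gestational diabetes and the glucose values at the oral glucose tolerance test (OGTT). Planned analyses uses such variables for description and to define subgroups (BMI, timing, OGTT result). Adjustment is mentioned only under Cost-effectiveness, where LGA is also an effect measure and regression may adjust for confounders if needed.

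The Questionnaires section says "Mood will be scored using the Edinburgh Postnatal Depression Scale (EPDS) at inclusion and post-partum". The scale is not in Table 2 and has no analysis of its own. The general rule for continuous data is a t-test or Mann-Whitney test.

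**The concern.** Blocking within centre keeps the arms balanced in each centre, so differences in LGA risk between centres contribute almost nothing to the treatment contrast. An unstratified standard error still counts them as noise, so the interval is a little too wide if centres differ. They may well differ, because women are recruited from both hospital and community midwife care. The same reasoning applies to baseline variables that predict LGA: using them removes outcome variation that the crude analysis leaves in.

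There is little power to spare. With 490 analysed per arm, power is 79.8% (pooled variance) to 80.1% (unpooled). There is also a matter of coherence: LGA could be reported adjusted in the economic evaluation and unadjusted in the main report. In an open-label trial, a covariate set chosen after outcomes are seen would invite doubt.

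**Working it through.** **1. Reproducing the stated sample size.** Inputs: "alpha-error 5% for 80% power" (abstract, Methods); "background incidence of 16% LGA (instead of the earlier 14%) in untreated women", "a reduction of LGA to 10% in participants who are treated" and "a 5% correction for women who are lost to follow up" (Sample size). Sidedness is not stated; two-sided is assumed.

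Unpooled formula: n = (1.96 + 0.8416)² × (0.16×0.84 + 0.10×0.90) / 0.06² = 7.849 × 0.2244 / 0.0036 = 489.3, so 490 per arm. Then 490 / 0.95 = 515.8, so 516 per arm and 1032 in total, as stated. The pooled-variance version gives 492, then 518 per arm (1036). The planned crude test and the stated sample size therefore agree.

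**2. Centre alone, by hand.** With mean LGA risk p = 0.13, p(1−p) = 0.113. A between-centre logit SD of s explains about s² × p(1−p) of the outcome variance:
- s = 0.3: 0.09 × 0.113 = 1.0%, so the interval is about 0.5% too wide.
- s = 0.5: 0.25 × 0.113 = 2.8%, so it is about 1.4% too wide.

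**3. Simulated power.** Assumptions: 980 analysed women, 25 centres of unequal size, blocks of 2 and 4 within centre, 16% v 10%, and one baseline score. Three analyses were run on the same data: crude chi-square; a Cochran-Mantel-Haenszel (CMH) test stratified by centre; and a marginal relative risk standardised from a logistic model containing the score but not centre.

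| Logit SD, centre / score | Trials | Crude | CMH by centre | Score-adjusted |
|---|---|---|---|---|
| 0 / 0 | 2000 | 80.1% | 80.2% | 79.8% |
| 0.3 / 0 | 2000 | 80.8% | 81.1% | 80.5% |
| 0.5 / 0 | 5000 | 80.4% | 81.2% | 80.0% |
| 0.3 / 0.5 | 5000 | 80.4% | 80.8% | 81.0% |
| 0.3 / 0.8 | 5000 | 81.1% | 81.3% | 82.9% |
| 0.3 / 1.0 | 5000 | 80.9% | 81.4% | 84.0% |

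Stratifying by centre gains 0 to 1 point. The score gains 0.6, 1.8 and 3.1 points as its SD rises from 0.5 to 1.0 (AUC about 0.64, 0.71 and 0.75). A score that predicts nothing costs 0.3 to 0.4 points in these runs. A further simulation, also with 980 women and 25 centres, adjusted for centre and one score together and again gained about 1 to 3 points. A run with 30 centres, centre SD 0.5 and a log odds ratio of 0.8 per SD went from about 80% to 84%, but it does not separate centre from covariate.

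**4. In terms of sample size.** The ratio of squared mean standard errors of the log relative risk (2000-trial runs), times 1032:
- SD 0.5: (0.1698/0.1718)² = 0.977, equivalent to 1008 women.
- SD 0.8: (0.1664/0.1720)² = 0.936, equivalent to 966 women.
- SD 1.0: (0.1640/0.1726)² = 0.903, equivalent to 932 women.

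The adjusted analysis would match the crude precision of 1032 women with 2% to 10% fewer.

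**5. Type I error.** Over the same six settings with no treatment effect (2000 trials each), rejection rates were 4.1% to 5.4% crude, 4.1% to 5.7% for CMH and 4.0% to 5.3% score-adjusted. The Monte Carlo standard error is √(0.05×0.95/2000) = 0.5 points, so there is no sign of inflation in any of them.

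**6. Depression score.** Analysis of covariance (ANCOVA) multiplies the residual variance by 1 − r². An assumed correlation of r = 0.5 between the inclusion and postpartum scores gives 0.75, a 25% reduction. At r = 0.25 it is 1 − 0.0625, about 6%. The documents give no value for r.

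**The case against.** The case for leaving the plan alone is substantial. Under 1:1 randomisation the crude relative risk is a valid marginal estimate. It is simple, it matches the sample-size calculation, and it avoids sparse strata. The number of centres is not stated. With 25 assumed, there would be about 980/25 = 39 women and 0.13 × 980 / 25 = 5 LGA births per centre on average, and fewer in small centres. Eligibility limited to a narrow glucose band, and largely risk-based testing, restrict the range of the predictors. An adjusted analysis may also be set out in a statistical analysis plan that is not shown. All of this stands, and it limits the point to efficiency. It does not remove the point: the article names the estimator, the test and the fallback test, which is a stated choice and not a gap.

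A reader might infer more than the documents support:
- **That the crude test is invalid or leaves the trial underpowered.** It holds its type I error and delivers the stated 80%.
- **That ignoring centre is the main loss.** Centre alone is worth 0 to 1 point; most of the gain comes from covariates.
- **That the predictors are known to be strong.** No figure for their strength is given.
- **That centres extend to tertiary hospitals.** That term describes only the RESPECT cohort under Sample size; this trial's settings are given as hospital and community midwife care.
- **That previous LGA is a separate recorded field.** It appears within one combined item in the guideline's list of risk factors, and the case record form is not shown.

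**Conclusion.** The point holds as a modest efficiency loss in a stated analysis choice, not as an error. Randomisation is stratified by centre, and the fixed primary test uses neither centre nor the collected baseline data. The likely gain is about 0 to 1 point of power from centre and about 1 to 3 points from covariates, the latter equal to roughly 2% to 10% of the sample size. These sizes rest on assumed between-centre logit SDs of 0.3 to 0.5, an assumed baseline score with logit SD 0.5 to 1.0, and an assumed 25 centres. If the covariates predict LGA weakly, the gain is close to nil. The point about the depression score is conditional: it matters only if the postpartum score is compared between arms.

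**What to change.** Before outcomes are examined, prespecify as the primary analysis a marginal relative risk for LGA, reported with the risk difference, adjusted for:
- centre, with small centres pooled by a stated rule or centre fitted as a random effect;
- a short fixed list of collected variables, such as prepregnancy BMI, parity and fasting OGTT glucose, plus previous LGA if it is recorded separately.

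Either modified Poisson regression with robust errors or standardisation from a logistic model will serve. Keep the crude relative risk and chi-square test as a sensitivity analysis. Using the same covariates for LGA in the economic evaluation would remove the open-ended adjustment there. If the postpartum depression score is compared between arms, adjust it for the inclusion score by ANCOVA.

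The core list needs no new data. The cost is a change of wording in the protocol and analysis plan, a pooling rule and a little code. Because the primary analysis is already published, the change should go to the ethics committee as an amendment, by the route given under Ethics and dissemination.

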**Fig. 1 Fig1:**
[figure not shown]
Consort flow diagram

Women are eligible if they have a singleton pregnancy, with a gestational age between 16 + 0 and 32 + 0 weeks at study entry, aged *≥* 18 years, without pre-conceptional diabetes, a major fetal congenital abnormality, or significant medical or psychiatric co-morbidities as judged by the investigator (e.g., high dose corticosteroid treatment), with the ability to understand the informed consent form. In addition, participants will need to have undergone a 2- or 3-point 75-gram OGTT, consisting of a fasting, 1 h (in case of 3-point OGTT) and 2 h post load glucose concentration via venipuncture, conducted between gestational ages 16 + 0 and 30 + 0 weeks yielding glucose concentrations discordant between the old WHO (1999) and the new WHO (2013) criteria.

A discordant result is defined as any single blood glucose concentration during a 75-gram venous blood OGTT within the following ranges, in the absence of any other glucose concentration exceeding the upper limit of discordancy (Table 1). For example, a pregnant individual is eligible if she has a fasting glucose between 5.1 mmol/l and 7.0 mmol/l, as long as the 2-hour glucose is below 8.5 mmol/l. Similarly, a pregnant individual with a 2-hour glucose between 7.8 mmol/l and 8.5 mmol/l is eligible, as long as the fasting glucose is < 7.0 mmol/l.

**Table 1 Tab1:** Glucose cut of values

	WHO 2013	WHO 1999
Fasting glucose	≥ 5.1 mmol/l	< 7.0 mmol/l
1-hour glucose	≥ 10 mmol/l	
2-hour glucose	< 8.5 mmol/l	≥ 7.8 mmol/l

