As recommended by the Guideline ‘Diabetes in Pregnancy’ of the Dutch Society of Gynaecology and Obstetrics (NVOG) and the Royal Dutch Organisation of Midwives (Koninklijke Nederlandse Organisatie van Verloskundigen (KNOV)), obstetricians and midwives in the Netherlands screen for GDM between 24 and 28 weeks gestational age (or 16 weeks of gestation in case of history of GDM) using a risk-based, 1-step screening strategy [6]. Risk factors for GDM are defined in the guideline as: family history of diabetes mellitus in a first degree relative; history of GDM, history of LGA or macrosomia > 4.5 kg; obesity (body mass index (BMI) > 30 kg/m^2)^; polycystic ovarian syndrome (PCOS); ethnicity (established by self-identification) associated with high GDM prevalence (e.g. Afro-Caribbean, Hindu-Surinamese, South-Asian, Middle-Eastern, Moroccan, Egyptian) and a history of unexplained stillbirth. Furthermore, clinical symptoms (e.g. polyuria, polydipsia, suspected macrosomia and/or hydramnios) suggestive of diabetes, are to trigger an oral glucose tolerance test.

Although there is wide uptake of the risk factor-based screening strategy in the Netherlands, clinicians are at liberty to apply different screening strategies at their discretion or upon patient request, without affecting eligibility.

The study will be executed in healthcare settings with both mid/high risk pregnancies (hospital antenatal care) and low risk pregnancies (community midwife antenatal care).

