#### Secondary outcomes

Secondary outcomes will include all outcomes defined in the core outcome set for studies of gestational diabetes mellitus prevention and treatment; Table 2 [29].

**Table 2 Tab2:** Secondary outcome

Gestational age at time of inclusion	In weeks and days
Adherence to the intervention	Did participants complete treatment according to allocation group until delivery: yes/no
Hypertensive disorders of pregnancy	Pregnancy induced hypertension, Pre-eclampsia (defined as by the ISSHP(30)), HELLP (Hemolysis, Elevated Liver enzymes, Low Platelets)
Requirement and type of pharmacological therapy for hyperglycaemia	If yes, oral medication, insulin, other
Gestational weight gain	In kilograms
Mode of birth	Spontaneous, assisted vaginal, caesarean (if instrumental: fetal distress or failure to progress)
Gestational age at birth	In weeks and days
Birth weight	In grams
Small for gestational age	Defined as birth weight < 10th centile, using the Dutch Perined reference charts, according to Hoftiezer(28)
Preterm birth	< 37 weeks (0 days) gestational age
Neonatal glucose postpartum	As a continuous outcome measure and as dichotomous outcome: moderate, glucose < 2.6 mmol/l; severe, glucose < 2.0 mmol/l(6)
Neonatal intravenous glucose	Yes/no
Stillbirth	Yes/no
Neonatal death	Yes/no
Secondary outcomes we will report in addition to the core outcome set:	
Macrosomia	Birth weight > 4500 g
Reason for preterm birth	Medically indicated or spontaneous contractions and/or spontaneous rupture of membranes
Onset of labour	Spontaneous, planned Caesarean section, induction of labour
Method(s) of induction of labour	Foley catheter/mechanical, prostaglandines, amniotomy, oxytocin, other (more than one optional)
Postpartum hemorrhage	> 1000 ml blood loss
Puerperal sepsis requiring antibiotics	Yes/no
Maternal admission postpartum	Yes/no, if yes: duration in days
1-min Apgar score, 5-min Apgar score, 10-min Apgar score	
Shoulder dystocia	Yes/no
Birth injury	i.e. fractures, nerve palsy
Cord blood C peptide	In a subset, where available
Neonatal intensive care/medium care admission	Yes/no, if yes: duration in days.
Hyperbilirubinemia	Yes/no
Respiratory support > 24 h	Yes/no
Neonatal encephalopathy	Yes/no
Other:	serious health outcomes up to the time of primary hospital discharge assessed from patient medical records(31)

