#### Baseline characteristics

Maternal baseline characteristics will be collected from the electronic patient file. We will provide a tabular presentation of the following baseline characteristics of both allocation groups, as well as the outcome variables: prepregnancy BMI (in kg/m^2^) and BMI at study entry, maternal age, parity, systolic and diastolic blood pressure at baseline and at study entry, intoxications (smoking, alcohol use), risk factors for GDM, reason for GDM screening, history of psychological problems, conception: spontaneous, fertility treatment (clomifene citrate, gonadotropins, IVF, ICSI), blood glucose concentrations at OGTT, gestational age at time of OGTT.

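### Gestational weight gain is compared without adjustment, although baseline measures that would sharpen the comparison are already collected: a small, avoidable loss of precision on one secondary outcome

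*Protocol article*

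**What the plan says.** Under Secondary outcomes, Table 2 of the protocol article lists "Gestational weight gain", measured in kilograms. It stands above the row that opens the outcomes added to the core outcome set, so it is a core-set outcome. The table does not say from when to when the gain is measured.

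Under Planned analyses, one rule covers all continuous outcomes: "tests for significance are t-tests or Mann-Whitney U tests, respectively". For data that are not normally distributed it adds: "The Hodges-Lehman estimator will be used to calculate the confidence interval for the difference in medians". No baseline covariate is named for any clinical outcome. Adjustment is mentioned only for the economic evaluation (Cost-effectiveness section).

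Under Baseline characteristics, the trial collects "prepregnancy BMI (in kg/m^2^) and BMI at study entry". Women are eligible "with a gestational age between 16 + 0 and 32 + 0 weeks at study entry" (Participants and eligibility criteria). The same section places routine screening at 24 to 28 weeks, or at 16 weeks after earlier gestational diabetes. Randomisation is 1:1, stratified by centre only.

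**The concern.** For most continuous outcomes, baseline adjustment is an optional refinement. Weight gain is a special case if it is counted from before pregnancy, because part of the outcome is then fixed before allocation. A plain two-group test leaves the between-woman variation in that part inside the comparison, and a chance imbalance in it at entry carries into the estimate. Stratifying by centre does not prevent this.

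At stake is the width of the confidence interval for an outcome that shows directly whether the dietary component had an effect. A modest real difference could be missed that the same women and the same data would have shown under a better analysis.

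**Working it through.** **1. The plan's own figure.** The article states a sample size only for the primary outcome. For 16% versus 10%, two-sided 5% (sidedness assumed), 80% power and unpooled variance:

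n per arm = (1.960 + 0.842)² × (0.16×0.84 + 0.10×0.90) / 0.06² = 7.849 × 0.2244 / 0.0036 = 489.3, rounded up to 490.

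With 5% loss to follow-up, 490/0.95 = 515.8, so 516 per arm and 1032 in total, as stated. This does not bear on weight gain directly, but it gives 490 evaluable women per arm for what follows.

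**2. How much of the gain precedes entry.** The article does not say. I assume 0.5 to 2 kg gained by week 13, then 0.25 to 0.4 kg per week to birth at week 39.

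Share before entry at week g = [g₁ + w(g − 13)] / [g₁ + 26w], with g₁ the gain by week 13 and w the weekly rate.

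| Entry week | Share of gain before entry |
|---|---|
| 16 | 16–32% |
| 24 | 45–56% |
| 28 | 60–68% |
| 32 | 74–79% |

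Example: week 24 with g₁ = 0.5 and w = 0.4 gives 4.9/10.9 = 45%.

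**3. Effect of adjustment on precision.** Let ρ be the correlation of gain at entry with the outcome, given gestational age at entry. The residual SD is SD × √(1 − ρ²), and the difference detectable at 80% power is 2.80 × SD × √(1 − ρ²) × √(2/490). SD and ρ are assumptions. For SD 6 kg:

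| ρ | 95% CI half-width (kg) | Detectable difference (kg) | Power for 1 kg | Variance removed | Equivalent sample |
|---|---|---|---|---|---|
| 0 (planned) | 0.75 | 1.07 | 74% | – | 1.00 |
| 0.3 | 0.72 | 1.02 | 78% | 9% | 1.10 |
| 0.5 | 0.65 | 0.93 | 85% | 25% | 1.33 |
| 0.7 | 0.54 | 0.77 | 96% | 49% | 1.96 |

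For SD 5 to 7 kg, the unadjusted detectable difference is 0.89 to 1.25 kg; at ρ = 0.7 it is 0.64 to 0.89 kg.

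**4. Which ρ is plausible.** Suppose gains before and after entry are uncorrelated, with SDs proportional to their shares f and 1 − f. Then ρ = f / √(f² + (1 − f)²).

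- f = 0.2: ρ = 0.24, 6% of the variance removed.
- f = 0.4: ρ = 0.55, 31% removed.
- f = 0.5: ρ = 0.71, 50% removed.

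A positive correlation between the two parts would raise these values. The gain in precision is therefore slight for entry near 16 weeks and considerable for entry in the usual screening window.

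**The case against.** The strongest reply is that nothing here is wrong. The unadjusted test is valid, gain before entry is balanced in expectation by randomisation, and chance imbalance is already covered by the 5% type I error. The trial is powered for another outcome. All of this stands.

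Second, counting from before pregnancy is an inference. If gain were counted from study entry, the argument from an already fixed part would fall away. This also stands, and it is why the start and end points should be stated. Collecting prepregnancy BMI makes the inference the likely one.

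Third, covariates for one secondary outcome are often left to the statistical analysis plan, and the article is a condensed text. That limits the weight of the point but does not remove it: the article names the test, so an adjusted main analysis would depart from it.

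Fourth, BMI is named at entry, not weight, and a last antenatal weight is not mentioned. BMI requires weight and height, however, and any analysis of gain up to delivery needs a late weight.

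Two stronger readings are tempting, and the article supports neither:

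- A reader might infer that most of the gain always precedes randomisation. The article gives no such share, and the assumed patterns contradict it for entry at 16 to 20 weeks. The fraction of gestation elapsed is not the fraction of weight gained.
- A reader might infer that the 16-week entry window itself adds noise to total gain. It does not. Later entry moves weight from the part after entry to the part before it and leaves the total essentially unchanged. The window does blur the raw correlation between gain at entry and total gain, which is why gestational age at entry belongs in the model.

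**Conclusion.** The point holds as a question of efficiency. The article fixes an unadjusted comparison for an outcome that, on its likely definition, is partly determined before allocation, and it leaves unused two baseline measures that would sharpen the comparison. There is no bias and no inflated error rate.

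Under the assumed SD of 6 kg, the detectable difference improves by 0.05 kg (ρ = 0.3) to 0.30 kg (ρ = 0.7), which is worth between 10% and 96% more participants for this one outcome. The conclusion rests on gain being counted from before pregnancy, on entry BMI being measured close to randomisation, and on the assumed SD and correlations. The importance is minor.

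**What to change.** Under Planned analyses, add a sentence for gestational weight gain that does the following:

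- States the start and end points of the gain (for example, last antenatal weight minus prepregnancy weight).
- Makes the main analysis a linear model with arm, weight gained from before pregnancy to study entry, and gestational age at entry. Prepregnancy and entry weight (or BMI), entered together, could replace the gain to entry.
- Reports the adjusted mean difference with its 95% CI as the result, and the raw group means as description.

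Length of gestation after randomisation should not be a covariate, because treatment may change it, for instance through induction of labour.

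The cost is a sentence of wording and a few lines of code, with no new visits or participants. The small downside is that women without an entry weight need a simple baseline imputation. The sentence should be settled before outcome data are compared by arm, so that the adjustment is not a post hoc choice.
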